### Assessment of efficacy

The smoking outcome measure used to estimate efficacy will be self-reported, prolonged abstinence from smoking from 4 weeks after randomisation until late pregnancy, validated by exhaled CO and/or saliva cotinine estimation. Smoking up to five cigarettes during the abstinence period will be permitted and consistent with a positive outcome.

### Assessment of safety

As this evaluation concerns a behavioural intervention we are not assessing any safety variables or collecting any adverse events.

### Procedures for missing, unused and spurious data

Our primary analyses will use an intention-to-treat approach, analysing all participants’ outcome data within the intervention group to which they were randomised, assuming, as is consistent with the Russell Standard, that participants with missing smoking status data are smoking [13]. Participants are advised to withdraw from the study if they have a miscarriage or still birth or where the infant has died following birth; however, if they do not and this is established at follow-up they may decline to provide information. These women will be included in the analyses and assumed to be smoking.

For the descriptive analyses, where there are missing baseline socio-demographic data, a separate category will be created and reported to represent the missing data. For statistical analyses involving socio-demographic variables with missing data, if the proportion of missing data is <5% and roughly similar in both intervention groups, then we will explore the robustness of using a complete-case analysis and an analysis including allowing for the missing data through analysing missing data as a separate category. If >5% of socio-demographic data are missing, then we will consider using imputation methods, such as multiple imputations. The impact of the imputations methods will be assessed fully in sensitivity analyses.

### Definition of populations analysed

For the efficacy and cost-effectiveness estimate assessments, all randomised participants will be used in the analyses using intention-to-treat population as defined below. All participants in the intention-to-treat population will be used for establishing use of NHS smoking cessation support and for the mechanism of effect analysis.

### Intention-to-treat population

The intention-to-treat (ITT) population is defined for this trial as all pregnant smokers who were randomised into the trial. Participants will be analysed based on the intervention group to which they were randomised. For participants with missing smoking-related outcomes, we will use the Russell Standard, where these participants will be assumed to be smoking [13].

### Sensitivity analyses

Two populations will be used for the sensitivity analyses on the 4-week and late-pregnancy smoking outcome measures:All pregnant smokers who were randomised into the trial, and who have outcome data available for analysis (complete case analysis). Participants will be analysed based on the intervention group to which they were randomised.All pregnant smokers who were randomised into the trial, and who, in the intervention group, self-reported at follow up that they received the intervention leaflet and text messages (per protocol analysis).

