### Adherence

Participants allocated to receive the MiQuit intervention will have an adherence check performed at the late pregnancy/postnatal follow-up stage, at 36 weeks gestation (visit 3). At this stage participants will be asked basic questions about their use of the texts sent.

If they wish, participants in both groups will be able to access additional support to help them stop smoking; they will all be asked about any use of support at each contact.

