### Visit 3 - late pregnancy/postnatal follow-up

*At 36 weeks gestation*: Participants will be asked to complete a questionnaire (data to be collected up to 10 weeks after estimated delivery date will be acceptable for use). This will include quality of life information (EQ-5D) and measures of smoking behaviour, attitudinal/behavioural information, use of NHS smoking cessation support and participants’ ratings of the intervention (MiQuit arm only). As for the 4-week visit, this visit will be performed mainly via telephone by a member of the study team at the co-ordinating centre, blind to treatment allocation. As for the 4-week visit, previously-described alternative methods will be employed to elicit the best response rate.

It is recognised that asking about the intervention at follow-up will result in the researcher who conducts the late pregnancy follow-up becoming un-blinded. To ensure that this has minimal impact on follow-up data obtained, the participants will be asked items about the intervention at the end of the interview/questionnaire starting with the question ‘*Did you receive any stop smoking text messages from the study team*?’

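### The per-protocol population sets a follow-up condition on the MiQuit arm only; if missing counts as smoking there too, the comparison is tilted towards MiQuit

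*Protocol article*

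**What the plan says.** The Sensitivity analyses section names two populations, both to be used for the 4-week and the late-pregnancy smoking outcomes.

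- Complete case: "All pregnant smokers who were randomised into the trial, and who have outcome data available for analysis (complete case analysis". The condition applies to both arms.
- Per protocol: all randomised women "who, in the intervention group, self-reported at follow up that they received the intervention leaflet and text messages (per protocol analysis". The condition applies to the MiQuit arm only. Controls are sent the same leaflet (Control section) but face no receipt or response condition.

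On when receipt becomes known, the Adherence section says that MiQuit participants "will have an adherence check performed at the late pregnancy/postnatal follow-up stage, at 36 weeks gestation (visit 3". The Visit 3 section puts the receipt question, "Did you receive any stop smoking text messages from the study team", at the end of the late-pregnancy interview or questionnaire. Table 1 lists the MiQuit-only items at visit 3 alone, and the Visit 2 section lists no receipt item.

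On missing outcomes, the section on missing, unused and spurious data says that, for the primary analyses, it is assumed that "participants with missing smoking status data are smoking". The Intention-to-treat population section repeats the rule: "For participants with missing smoking-related outcomes, we will use the Russell Standard, where these participants will be assumed to be smoking". Neither section mentions the per-protocol population.

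**The concern.** A MiQuit woman with no late-pregnancy follow-up cannot report receipt and so cannot enter the per-protocol set. A control woman in the same position remains in it. If she is then counted as a smoker, the women who are smokers by assumption leave the denominator in one arm and stay in the other. The MiQuit quit rate is divided by the follow-up fraction and the control rate is not, whether or not the texts work.

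The definition also governs the 4-week outcome. A MiQuit woman with 4-week data but no late-pregnancy follow-up is removed from the 4-week comparison because of something that happened afterwards; a control woman is not.

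Estimating effectiveness is a secondary objective, and the sample size section says that evidence of likely effectiveness would help in obtaining funds for a definitive trial. A sensitivity analysis that leans in a known direction could be misread as support for the main result.

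**Working it through.** **Inputs from the protocol article**

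- 200 women per arm (Tables 2-5).
- Control quit rate in late pregnancy: 5% to 10% (Estimating cessation in late pregnancy).
- Odds ratios planned for: 1.3 to 1.8 (Estimates for treatment effect).
- Follow-up rate: not given. The Background says follow-up rates still need determining. Assumed here: 60% to 90%, equal in both arms.

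**The plan's own figure first.** Table 4 gives 0.82 to 2.76 for an odds ratio of 1.5 at a 10% control rate. With 20/200 control quitters, the MiQuit odds are 1.5 × 20/180 = 0.1667, a rate of 14.29%, or 28.57/200. The standard error of the log odds ratio is √(1/20 + 1/180 + 1/28.57 + 1/171.43) = 0.3105. Then exp(ln 1.5 ± 1.96 × 0.3105) = 0.82 to 2.76, as printed. The article states no per-protocol figure.

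**Expected per-protocol odds ratio with no true effect.** Let q be the quit rate in each arm with missing counted as smoking, and r the follow-up fraction. Quits are seen only among responders, and for now every MiQuit responder is taken to report receipt.

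- Control: 200q quitters among 200, rate q.
- MiQuit: 200q quitters among 200r, rate q/r.
- OR = [(q/r)/(1 − q/r)] / [q/(1 − q)] = (1 − q)/(r − q).

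| Follow-up r | q = 5% | q = 10% | MiQuit rate at q = 10% |
|---|---|---|---|
| 90% | 0.95/0.85 = 1.12 | 0.90/0.80 = 1.13 | 20/180 = 11.1% |
| 80% | 0.95/0.75 = 1.27 | 0.90/0.70 = 1.29 | 20/160 = 12.5% |
| 70% | 0.95/0.65 = 1.46 | 0.90/0.60 = 1.50 | 20/140 = 14.3% |
| 60% | 0.95/0.55 = 1.73 | 0.90/0.50 = 1.80 | 20/120 = 16.7% |

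**Chance of a nominally significant result with no true effect** (200,000 simulated trials per setting, chi-squared test, two-sided 5%):

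| Follow-up r | q = 5% | q = 10% |
|---|---|---|
| 90% | 5.7% | 6.5% |
| 80% | 8.4% | 11.9% |
| 70% | 13.7% | 23.1% |
| 60% | 23.2% | 41.8% |

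**Same response condition in both arms.** Both rates become q/r, the odds ratio is 1.00, and the simulated two-sided error is 4.9% to 5.1%.

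**If some MiQuit responders report non-receipt.** Take q = 10%, r = 80%, and 10% to 20% of responders excluded for non-receipt. If the excluded women quit as often as the other responders, the odds ratio stays at 1.29. If they quit half as often it is 1.36 to 1.45; if twice as often, 1.15 to 1.05. With the response condition applied to both arms, the same cases give 1.06 to 1.13 and 0.90 to 0.81. That residue is selection on reported receipt, which the response condition does not remove.

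**The 4-week outcome.** The formula does not carry over. A MiQuit woman who had quit at 4 weeks and was lost later leaves the numerator as well as the denominator, so the inflation may be smaller. The article gives nothing from which to size it.

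**The case against.** The strongest objection is that the key premise is inferred. The rule that missing means smoking is written for the primary analyses and under the intention-to-treat heading. The article defers detail to a full statistical analysis plan, which is not at hand. If control non-responders were also dropped from the per-protocol set, the denominator bias would vanish. This stands, and the size above is therefore conditional. It does not remove the point: the definition as written keeps all randomised controls, and only the complete-case item limits both arms to observed outcomes.

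The size also depends on a follow-up rate that the article does not give. At 90% follow-up the bias is small.

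A reader might infer that MiQuit will look effective when it is not, or that the trial's efficacy estimate is compromised. The documents support neither. The first presumes both a true null and substantial loss. As to the second, the Definition of populations analysed section assigns the efficacy and cost-effectiveness estimates to the intention-to-treat population. The trial is a pilot with no single primary outcome, and no decision rule uses the per-protocol result. The complete-case analysis would stand beside it and, under the same null, gives an odds ratio of 1.00, so a divergence would be visible.

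**Conclusion.** The one-sided condition is explicit and should be corrected. Provided that missing counts as smoking in this population, that follow-up is equal in the two arms, and that reported receipt is unrelated to quitting, a MiQuit with no effect gives an expected late-pregnancy odds ratio from about 1.12 (90% follow-up) to 1.80 (60%). Follow-up of 60% to 80% alone would produce roughly the 1.3 to 1.8 range that the trial plans around.

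The 4-week comparison shares the defect, but a reader should not apply these figures to it. Only one of two sensitivity analyses is affected, so this is a moderate issue.

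**What to change.** 1. Apply the same response condition to both arms: MiQuit and control women enter the per-protocol set only with a completed late-pregnancy follow-up, by any of the permitted modes. This removes the denominator bias under equal follow-up and needs no new data.
2. State how missing outcomes are handled in this population, separately for the 4-week and late-pregnancy outcomes.
3. Report that selection on self-reported receipt remains in the MiQuit arm, and read the result with that in mind.

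The cost is a few lines of wording, settled before the data are analysed.

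Optional: where MiQuit system data allow, define receipt of texts from them instead of from self-report. The article mentions process variables, STOP texts and tailoring data held on a server, but does not state that a full message log exists for every woman, and such data could not show receipt of the leaflet. A complier estimate that uses randomisation as the instrument could be added; it answers a different question and is not needed to correct this one. A leaflet-receipt condition for controls is not proposed: no such question is shown, and 385 women had been recruited by 27 August 2014.

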### Health economics

Per-participant costs of providing the MiQuit service will be calculated. and EQ-5D data will be used with this to estimate the incremental cost-effectiveness of offering the MiQuit intervention. Given that this is a pilot study rather than a definitive trial, it is acknowledged that the estimate for incremental cost-effectiveness will have limited accuracy and so a range of different potential values will be used to model the potential lifetime cost effectiveness of introducing MiQuit into routine clinical practice. Modelling will use i) estimates for uptake of NHS services by smokers and non-smokers after pregnancy, which have been derived from a similar recent trial that employed post-partum follow up [18], and ii) a model, which values smoking cessation in pregnancy in economic terms and is currently being developed by a PhD student.

### Data management

Data will be entered electronically on a trial specific database. Only research midwives and the research study team will have database access, which permits them to make new entries and also to access relevant personal data collected from participants at their sites (for example, contact details).

To enable anonymisation, each participant will be assigned a unique trial identity code number, allocated at randomisation, for use on all trial documents and the electronic database.

The database will be maintained on a server located within the Nottingham Clinical Trials Unit, University of Nottingham (Chief Investigator’s institution). The database has a regular back-up routine, and will be password protected.

Anonymised data, which have been sent to MiQuit and which have been used to individualise SMS text messages, will be held on a secure server within the Institute of Public Health at the University of Cambridge. Only authorised trial staff shall have access to trial documentation other than for the regulatory requirements.

All trial staff and investigators will endeavour to protect the rights of the trial’s participants to privacy and informed consent and will adhere to the Data Protection Act, 1998.

Electronic data will be backed up every 24 hours to both local and remote media in encrypted format. Electronic audio files of the interviews will be stored in an encrypted format. Transcribed interviews will be anonymised.

Monitoring of trial data shall include confirmation of informed consent; source data verification; data storage and data transfer procedures; local quality control checks and procedures, back-up and disaster recovery of any local databases and validation of data manipulation. The Trial Manager, or where required, a nominated designee of the Sponsor, shall carry out monitoring of trial data as an on-going activity.

All records and documents regarding the conduct of the study will be retained for at least 7 years or for longer if required. The trial master file and trial documents held by the Chief Investigator on behalf of the sponsor will be archived at secure archive facilities at the University of Nottingham. This archive shall include all trial databases and associated meta-data encryption codes.

### Transport, storage and analysis of saliva samples

The use of oral fluid samples (saliva) is a non-invasive way of measuring cotinine, a nicotine metabolite [22]. Saliva samples will be collected at visit 4 (around 36 weeks gestation) to verify smoking status by a researcher or by post if a visit is not possible. Saliva samples will be obtained using clean salivettes; it will involve the participant placing a sterile swab under the tongue, for up to 5 minutes until it is moist and then placing the swab into a sterile vessel. All samples will be stored in a linked anonymised format in a secure freezer storage unit (−20°C) within Nottingham Health Science Biobank (NHSB) according to their approved protocols. Where researchers obtain samples by visiting participants who live at a distance that would make it impractical to deliver these to Nottingham in person, these samples will be posted by the study team in suitable packaging, and when received, the study team will transfer them to NHSB. Samples are stable at ambient temperatures for several days. For postal samples, the participant will be asked to state the date they provided the sample on the label. Participants will be advised to return the sample (using the protective pre-paid and addressed packaging) on the day they provide the sample. Again these will be transferred to the NHSB by a member of the study team. Nottingham Health Science Biobank has been given full approval by the HTA to be a full licence holder, meeting all legislation requirements.

Once all samples have been collected for the study, NHSB will arrange transportation of samples by courier to ABS Laboratories Ltd, Hertfordshire for analysis in a single batch shipment. The shipment will contain a complete inventory of all samples, along with the name of the person responsible for sending the samples. The master database to link all samples will be held by the Nottingham study team in a password encrypted file. The laboratory will quantify salivary cotinine levels using a quantitative enzyme immunoassay technique (EIA). Once the analysis has been completed the saliva samples will be destroyed in accordance with the Human Tissue Act 2004, this will only occur once the study team have received the results and have analysed the data to ensure that all samples remain in a normal range and do not require retesting.

### Dissemination

Results will be written up for publication in peer reviewed journals and disseminated at local, national, and international meetings where appropriate. A lay summary will be produced and distributed to those participants who have indicated they would like to receive a copy and other interested parties.

Participants will not be identified in any publications or presentations resulting from this study.

### User and public involvement

A Public and Patient Involvement representative has contributed to this protocol, to trial documents and to the development of the intervention. In addition, several individuals who took part in a pilot trial of MiQuit have been consulted and have provided guidance on the refinement and delivery of MiQuit.

### Indemnity

Insurance and indemnity for trial participants and trial staff is covered within the NHS Indemnity Arrangements for clinical negligence claims in the NHS, issued under cover of HSG (96)48.

The University of Nottingham as research Sponsor indemnifies its staff, research participants and research protocols with both public liability insurance and clinical trials insurance. These policies include provision for indemnity in the event of a successful litigious claim for proven non-negligent harm.

### Trial management

The Chief Investigator has overall responsibility for the study and will oversee all study management. The Trial Management Group (TMG) will be responsible for the day to day running of the trial. The TMG will be supported by and report to an independent Trial Steering Committee. Trial co-ordination will be managed centrally by the study team based in Nottingham led by a trial manager and guided by the TMG. The Cambridge research team will manage a server hosting the MiQuit intervention; however, the Chief Investigator (Nottingham) will be custodian of all study data.

### Ethics approval

Ethical approval for this study was granted by Nottingham 1 Research Ethics Committee (NRES reference 13/EM/0427).

### Sponsor

The trial is sponsored by the University of Nottingham.

## Discussion

Once completed, this pilot trial will provide the necessary data to plan for larger definitive study to investigate whether or not self-help cessation support [7] provided in an interactive text message format can help pregnant women to achieve cessation. This pilot trial provides information, which complements that from our earlier feasibility trial [11] and has been necessary for a number of reasons.

First, the primary outcome for the earlier study was self-reported, 7-day, point-prevalence, smoking cessation [12] measured at 12 weeks after trial entry [11]. Whilst any period of smoking cessation is likely to be beneficial for pregnant women and their infants, maximal health gain for infants is likely to occur if mothers maintain abstinence throughout pregnancy. Additionally, it is possible that women who remain smoke free for the whole of pregnancy will be better able to avoid relapse back to smoking after childbirth and, for both reasons, a definitive study should aim to detect any impact on women’s smoking throughout the whole of pregnancy. Most smoking cessation trials encourage participants to set a quit date and cessation outcomes are measured prospectively from this point; however, MiQuit is a ‘cessation-induction’ intervention, which encourages, but does not require users to set a definite quit date. Finding appropriate time points in pregnancy from which continuous cessation can be measured, monitored and validated, after participants have been exposed to MiQuit, is an important issue that the pilot trial is attempting to resolve. Achieving high ascertainment rates for piloted methods of measuring continuous cessation will mean that our piloted outcome could be used to measure and validate smoking cessation throughout the whole of pregnancy in any future definitive RCT.

Second, the treatment effects attributable to smoking cessation interventions are generally inversely proportional to their intensity [23] and MiQuit is a low-intensity intervention. For a definitive study to have sufficient power to show whether or not MiQuit has efficacy for smoking cessation in pregnancy, such a study could need a sample size of over 3,000 participants (estimated using data from previous MiQuit trial [11]). Clearly, to plan a definitive study that combines a sufficiently high chance of providing a definitive answer with efficient use of resources, the best possible information is needed. This pilot trial will provide the first estimate for the treatment effect that MiQuit might have for influencing continuous smoking cessation between earlier and later (approximately 36 weeks) pregnancy; although the pilot is not powered to provide such an estimate with high precision, it will nevertheless, be a very valuable parameter. Additionally, knowing the combined treatment groups’ cessation rates at 36 weeks will also be useful to inform definitive-trial sample size calculations.

Third, recruitment rates from this study will be vital for assessing the feasibility of delivering a large definitive RCT investigating smoking cessation in pregnancy and using English National Health Service (NHS) research structures. Since 2006, the English NHS has developed and revised research networks, funded from the health service budget and orientated towards delivering clinical research; there is a particular focus on RCTs that influence clinical practice [24]. Networks provide staff working across the NHS whose remit is to recruit to research studies and researchers who successfully access network staff support can efficiently deliver multi-centre RCTs. However, negotiating access to research networks and subsequently finding the most efficient ways of combining their efforts with those of a university-based research team can be challenging and, significantly the two most recent English pregnancy smoking cessation trials [18,19] were completed with relatively little research network input. To date, overall pilot trial recruitment has been strong and it appears that study methods could, feasibly be used to recruit to a larger definitive study. However, across the 16 trial centres from which this pilot recruits, there has been marked variation in recruitment rates. Consequently, lessons learned from our planned pilot trial process evaluation should help us to better understand the reasons for different recruitment rates in different centres and, potentially to enhance the research network staff experience of recruiting to the trial for any future study.

Given the nature of this pilot trial, discussion has principally focussed on methodological issues. However, if after this study, a definitive RCT is conducted and MiQuit is found to be effective for smoking cessation in pregnancy, this very cheap and likely (in that circumstance) highly cost-effective intervention could easily be made very widely available in many different ways to support smoking cessation in pregnancy.

